## **5. Protocol treatment**

---

### **1) Surgical resection**

Before pancreatic transection, concurrent division of the splenic artery using a mechanical stapler will not be permitted. A linear stapler, Endo GIA Reinforced Reload with Tri-Staple Technology (Black Cartridge, Covidien®), will be used in all patients. The pancreatic parenchyma will be compressed with the stapler at the planned line of resection for over 5 minutes before transection is performed. For the patients in Arm A, the splenic vein will be isolated from the pancreatic parenchyma and dissected after ligation. For those in Arm B, the splenic vein will be transected concurrently with the pancreatic parenchyma using the aforementioned stapler. Anti-coagulant treatment, such as low-molecular-weight heparin or fondaparinux, will be permitted at 48 hrs after surgery.

Antibiotics, plasma expanders, blood products, analgesic drugs, H2 blockers, and proton pump inhibitors will be used for intra- and postoperative management at the discretion of the surgeons. In addition, there are no regulations on the drugs used to control complications and adverse events. Prophylactic administration of octreotide will not be permitted.

### **2) Intraoperative photography**

To confirm that the surgical procedures are conducted as allocated at the time of central judgement, two photographs (before and after pancreatic transection) will be taken for all patients. Central judgement will be conducted biannually for all of the registered patients. At that time, the photographs will be reviewed by more than two members of the committee.

### **3) Chemotherapy and radiotherapy**

There are no regulations regarding the use of preoperative, intraoperative or postoperative chemotherapy or radiotherapy as treatments in this study. However, details including the treatment regimen and cycles given of the preoperative treatment are to be

reported in the case report form.

#### 4) Follow-up after surgery

The presence of thrombus in the splenic vein will be evaluated at 1 and 6 months after surgery by enhanced computed tomography or magnetic resonance imaging.

## 6. Study management

---

### 1) Monitoring

Central monitoring will be performed each year by the data centre to evaluate the study progress and ensure for study quality. The following aspects will be monitored: i) data accumulation; ii) patient eligibility; iii) severe adverse events; iv) protocol deviations; v) reasons for cessation or expiration of the protocol; vi) background factors of the patients; and vii) other problems concerning study progress and safety.

### 2) Audit

The person appointed by the audit office visits the participating institution and confirms the study implementation system, and whether the study is conducted in accordance with the study protocol and the ethical guidelines.

## 7. Ethical considerations

---

All investigators will conduct this study according to the Helsinki Declaration.

### 1) Informed Consent

All subjects for this study will be provided a consent form describing this study and providing sufficient information for subjects to make an informed decision about their participation in this study. The consent form will be submitted with the protocol for review and approval by the Institutional Review Board (IRB) for the study. The formal consent of a subject, using the IRB-approved consent form, must be obtained before that subject is submitted to any study procedure. This consent form must be signed by the subject, and the investigator-designated research professional obtaining the consent. A copy of the IRB-approved form must be kept on-site and by administrative office and data center.

### 2) IRB review

This protocol and any amendments will be submitted to a properly constituted independent IRB, in agreement with local legal prescriptions, for formal approval of the study conduct. The decision of the IRB concerning the conduct of the study will be made in writing to the investigator and a copy of this decision will be provided to administrative office and data center before commencement of this study.

## 8. Registration and Allocation

---

### 1) Facility registration

Approval of this protocol by the IRB of each institution is required. The research director of each institution send a copy of the approval letter of the IRB and a facility registration form by FAX to the administrative office (Wakayama Medical University).

### 2) Informed consent

The formal consent of a subject, using the IRB-approved consent form, must be obtained before that subject is submitted to any study procedure. This consent form must be signed by the subject.

### 3) Case registration

The investigator at each institution confirms the inclusion and exclusion criteria before surgery, and then registers the subject of the data center.

### 4) Registration number

After confirming that the conditions are satisfied, the registration number is issued and "registration" is completed at this point. If the input data is inadequate or does not meet the eligibility criteria, the registration number will not be issued and it will not be "registered".

### 5) Allocation

When the case registration is made, the assigned group (A group or B group) and "registration notice form" showing the registration number are displayed. The investigator shall start treatment after completion of registration.

### 6) Start of the protocol treatment

The research director or the investigator will start the protocol treatment within 28 days after registration after confirming the completion of the case registration with "registration notice form". If it is ineligible, the investigator explains to the subject that registration to this study is not possible.

Registration after the start of protocol treatment is not allowed without exception

## 9. Examination and observation parameters

---

### 1) Preoperative parameters

A) Height/Body weight/BMI

B) DM/Steroid use/Anticoagulant/Cardiac disorder

C) Preoperative treatment (chemotherapy・chemoradiotherapy)

D) Blood examination (WBC/Hb/PLT/T-Bil/Cre/Alb/Amy/HbA1c(NGSP))

- 258 E) Pancreatic thickness (Preoperative CT or MRI imaging)  
 259 F) MPD diameter  
 260 G) Original disease  
 261  
 262 2) Operative parameters  
 263 A) Operative procedure (Open or laparoscopic/DP-CAR/SPDP)  
 264 B) Conversion to open surgery from laparoscopic surgery  
 265 C) Lymph node dissection (D0-D3)  
 266 D) Concurrent arterial resection (celiac artery)  
 267 E) Operative time (min)  
 268 F) Blood loss (ml)  
 269 G) Blood transfusion (RBC/FFP)  
 270 H) Pancreatic texture (soft/hard)  
 271 I) Pancreatic cut line (Preoperative CT or MRI)  
 272 J) Cartridge number  
 273 K) Reinforcement sheet (coated/non-coated)  
 274 L) Drainage number and site  
 275 M) Intraoperative parameters of stapler  
 276 haemostasis of the staple line, integrity of the staple line, incidence of pancreatic injury,  
 277 need for additional sutures to securely close the pancreatic stump  
 278 N) Other staple-related adverse events  
 279

| Score | Integrity of the staple line | Haemostasis of the staple line | Pancreatic injury     |
|-------|------------------------------|--------------------------------|-----------------------|
| 0     | No                           | No                             | No                    |
| 1     | Yes                          | Compression or coagulation     | Injury for repair     |
| 2     |                              | Suture                         | Need for re-resection |

- 280  
 281 3) Postoperative parameters  
 282 A) POD1/3/7 Blood examination (WBC/Hb/Alb/Amy/CRP)  
 283 B) POD1/3 Drain amylase  
 284 C) Postoperative complications  
 285 D) POPF grade/POH/Mortality/Thrombosis or Obstruction of splenic vein (1 month/6  
 286 months)  
 287 E) Postoperative course  
 288 ● Drainage period  
 289 ● Postoperative hospital stay

290

291 4) Discontinuation parameters

292 ● Reason

293

## Study calendar

|                        | Pre-             |                   | Intra-                                                                               | Post-           |                       |                        |
|------------------------|------------------|-------------------|--------------------------------------------------------------------------------------|-----------------|-----------------------|------------------------|
|                        | Pre-registration | Post-registration |                                                                                      | Until discharge | 1 month after surgery | 6 months after surgery |
| Informed consent       | •                |                   |                                                                                      |                 |                       |                        |
| Registration           | •                |                   |                                                                                      |                 |                       |                        |
| Patient background     | •                | •                 |                                                                                      |                 |                       |                        |
| Blood examination      | •                | •                 |                                                                                      | •               |                       |                        |
| Operation              |                  |                   | •                                                                                    |                 |                       |                        |
| Drainage amylase level |                  |                   |                                                                                      | •               |                       |                        |
| Drainage removal       |                  |                   |                                                                                      | •               |                       |                        |
| Adverse events         |                  |                   | [figure not shown] |                 |                       |                        |
| CT/MRI                 | •                |                   |                                                                                      |                 | •                     | •                      |

## 10. Definition of complications

Defined as an event that occurred within 6 months after surgery

### 1) Postoperative pancreatic fistula (POPF)

International Study Group of Postoperative Pancreatic Fistula (ISGPF)

### 2) Delayed gastric emptying (DGE)

International Study Group of Pancreatic Surgeons (ISGPS)

### 3) Postpancreatectomy hemorrhage (PPH)

International Study Group of Pancreatic Surgeons (ISGPS)  
Wente MN, Veit JA, Bassi C, et al. Postpancreatectomy hemorrhage (PPH)-An International  
Study Group of Pancreatic Surgery (ISGPS) definition. Surgery 2007;142:0-25.

#### 4) Other complications

Clavien classification

Grade I: any deviation from the normal postoperative course but without any need for  
pharmacologic treatment or surgical, endoscopic, or radiologic intervention

Grade II: Requiring pharmacological treatment with drugs other than such allowed for  
grade I complications. Blood transfusions and total parenteral nutrition are also included.

Grade III: complications requiring surgical, endoscopic, or radiologic intervention

IIIa: intervention not under general anesthesia

IIIb: intervention under general anesthesia

Grade IV: life-threatening complications requiring intermediate or intensive care unit (ICU)  
management

IVa: single organ dysfunction (including dialysis)

IVb: multi organ dysfunction

Grade V: death

Suffix 'd': If the patients suffers from a complication at the time of discharge, the suffix "d"  
(for 'disability') is added to the respective grade of complication. This label indicates the need for  
a follow-up to fully evaluate the complication.

Dindo D, Demartines N, Clavien PA. Classification of surgical complications: a new proposal  
with evaluation in a cohort of 6336 patients and results of a survey. Ann Surg.  
2004;240:205-13.

## **11. Report of adverse events**

---

### 1. Report of adverse events

If "serious adverse event" or "unexpected adverse event" occurs, the research director of the  
institution reports to the administrative office (Wakayama Medical University).

1) Leading to death

2) Life threatening

3) Requiring hospitalization or prolongation of hospital stay

4) Leading to everlasting or serious malfunction

5) Leading to congenital malformation or deficiency

### 2. Expedited report of adverse events

1) All deaths "during protocol treatment" or "within 30 days after protocol treatment"

2) Unexpected Grade IV adverse events

An adverse event that is judged to be causally related to protocol treatment shall be subject to  
expedited report.

If an adverse event to be subject to expedited report occurs, the investigator shall report to Wakayama Medical University by e-mail within 48 hours. Wakayama Medical University distributes emails about this adverse events to the research director of each institution to share information. The principle investigator will report to the Efficacy and Safety Evaluation Committee as soon as possible, and ask the judge about the adequacy of response to the adverse event.

### 3. Normal report of adverse events

#### 1) Deaths after 31 days from the end of protocol treatment

Deaths suspected of treatment related death are applicable. Obvious original disease death does not apply.

#### 2) Expected Grade IV adverse events

#### 3) Unexpected Grade III adverse events

#### 4) Other serious medical events

## **12. Definition of endpoints**

---

### Primary endpoint

#### 1) Incidence of a clinically relevant POPF (ISGPF grade B/C)

Incidence of a clinically relevant POPF (grade B/C), according to the ISGPF criteria which is the evaluation criteria for POPF

### Secondary endpoints

#### 1) Operative time

Time from start of surgery to end of surgery

#### 2) Blood loss

Total blood loss during surgery

#### 3) Preoperative pancreatic thickness

Pancreatic thickness of estimated pancreatic cut end measured by preoperative CT or MRI

#### 4) Incidence of bleeding from staple line

Incidence to need additional hemostasis (including coagulation or suture) for bleeding of staple line after pancreatectomy of mechanical stapler

#### 5) Grade of bleeding from staple line

Grade to need additional hemostasis (including coagulation or suture) for bleeding of staple line after pancreatectomy of mechanical stapler

#### 6) Incidence of integrity of the staple line

Incidence of insufficient suture on staple line line after pancreatectomy of mechanical stapler

393

394

395

396 7) Incidence of pancreatic injury

397 Incidence of pancreatic injury on staple line during or after pancreatectomy of mechanical stapler

398

399 8) Grade of pancreatic injury

400 Grade of pancreatic injury on staple line during or after pancreatectomy of mechanical stapler

401

402 9) Incidence of additional suture for pancreatic stump

403 Incidence to need additional suture of staple line for hemostasis or repair after pancreatectomy of

404 mechanical stapler

405

406 10) Length of drain placement

407 Number of days from operation date to drain removal date (the peripancreatic drain to be removed

408 last)

409

410 11) Length of the hospital stay

411 Number of days from operation date to discharge date

412

413 12) Incidence of conversion from laparoscopic surgery to open surgery

414 Incidence of conversion to open surgery during laparoscopic surgery

415

416 13) Incidence of overall POPF (Grade A, grade B, and C)

417 Incidence of overall POPF of grade A, grade B, or grade C, according to the ISGPF criteria

418

419 14) Incidence of POPF grade C

420 Incidence of POPF grade C, according to the ISGPF criteria which is the evaluation criteria for

421 POPF

422

423 15) Incidence of postpancreatectomy hemorrhage (PPH)

424 Incidence of overall PPH, according to the ISGPS criteria

425

426 16) Incidence of overall postoperative complications

427 Incidence of overall postoperative complications, according to Clavien-Dindo classification

428

429 17) Incidence of 90-day mortality

430 Incidence of surgery-related deaths from operation date to postoperative 3 months

431

432 18) Incidence of thrombosis of splenic vein

Incidence of thrombosis of splenic vein by follow-up CT or MRI after 1month or 6 months after surgery

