## 1. Study purpose

---

**The aim of the COSMOS-DP trial is to establish the non-inferiority of the safety of resecting the splenic vein together with the pancreatic parenchyma compared with that of the conventional technique of isolating the vein from the pancreas before ligation and division during DP using mechanical staplers.**

The primary endpoint; the incidence of grade B/C PF

The secondary endpoints;

Outcome measures related to surgery; the operative time, blood loss volume, haemostasis of the staple line, integrity of the staple line, incidence of pancreatic injury, need for additional sutures to securely close the pancreatic stump, drainage duration, postoperative hospital stay duration and incidence of conversion from laparoscopic surgery to open surgery.

Outcome measures related to complications; the incidence of all grades of PF, incidence of grade C PF, incidence of intra-abdominal haemorrhage, incidence of all complications, mortality and the incidence of splenic vein thrombosis (1 and 6 months after surgery)

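### Secondary endpoint 17 is labelled 90-day mortality but defined as surgery-related deaths only, with no rule for relatedness, so the reported figure can fall below all-cause mortality

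*Protocol*

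**What the plan says.** Protocol Section 1 states the aim as "to establish the non-inferiority of the safety of resecting the splenic vein together with the pancreatic parenchyma", compared with the conventional technique. Its complication-related secondary outcomes include "incidence of all complications, mortality and the incidence of splenic vein thrombosis", with no restriction by cause of death. Section 9, postoperative parameters, item D, also lists mortality without qualification.

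Section 12 gives the operative definition. Secondary endpoint 17 is headed "Incidence of 90-day mortality", and the line beneath reads "Incidence of surgery-related deaths from operation date to postoperative 3 months". The text available contains no definition of surgery-related, no procedure for deciding it, and no named person or committee to decide it.

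Section 11 deals with adverse-event reporting. It lists events leading to death as serious, names all deaths during or within 30 days of protocol treatment for expedited report, and for later deaths says "Deaths suspected of treatment related death are applicable. Obvious original disease death does not apply".

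**The concern.** The label and the definition describe different quantities. A reader who sees 90-day mortality in a results table will take it to be deaths from any cause by day 90. The defined quantity is the subset attributed to surgery. It cannot exceed the all-cause count and can fall below it.

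Death from any cause needs no judgement; death related to surgery does. In a comparison of two surgical techniques with no blinding described, a causal judgement without a rule leaves room for knowledge of the arm to enter. Section 2 names the feared harm of the combined technique, bleeding from the splenic vein stump, so whoever classifies a death may expect a particular cause in one arm. Section 4 admits patients with pancreatic cancer and metastatic tumours, so deaths of arguable cause within three months are foreseeable.

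The protocol fixes this definition itself. It is not a detail left to a statistical analysis plan, and a plan that followed the protocol would carry the restriction forward.

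**Working it through.** **Stated figures.** The protocol gives no mortality rate, so there is none to reproduce. Its sample size concerns only grade B/C pancreatic fistula. With 10% in both arms, a margin of 0.09, one-sided alpha 0.05 and power 80%, n = (1.645 + 0.842)² × 2 × 0.10 × 0.90 / 0.09² = 137.4, which rounds up to the stated 138 per arm. Endpoint 17 plays no part in it.

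**Where deaths appear in the protocol.**

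| Place | Scope |
|---|---|
| Section 1, secondary endpoints | Mortality, no cause restriction |
| Section 9, postoperative parameter D | Mortality, no cause restriction |
| Section 12, endpoint 17, label | 90-day mortality |
| Section 12, endpoint 17, definition | Surgery-related deaths to 3 months |
| Section 11.1 | Serious events include those leading to death, no cause or time filter |
| Section 11.2 | All deaths on treatment or within 30 days after it; a sentence on causality follows the list |
| Section 11.3 | Later deaths only if suspected to be treatment-related |

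Only the definition of endpoint 17 restricts the endpoint by cause. Section 11 governs notification of adverse events to the administrative office and does not define what the endpoint counts.

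**Who judges relatedness.** Section 8, item 5, shows the assigned group when the case is registered, and the surgeon then carries out the allocated technique. The central judgement in Section 5, item 2, reviews photographs: "To confirm that the surgical procedures are conducted as allocated at the time of central judgement". It does not review deaths. Under Section 11.2 the Efficacy and Safety Evaluation Committee is asked whether the response to an event was adequate; no blinded ruling on cause is mentioned.

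**Direction and size.** Let D be all deaths by the cut-off and s the share classed as surgery-related. The endpoint counts sD and omits (1 − s)D, which is zero when s = 1. The documents give neither D nor s. The values below are assumptions, using 304 patients and expected D = 304 × rate.

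| Assumed all-cause rate | Expected deaths | Omitted, s = 100% | Omitted, s = 75% | Omitted, s = 50% |
|---|---|---|---|---|
| 0.5% | 1.52 | 0 | 0.38 | 0.76 |
| 1% | 3.04 | 0 | 0.76 | 1.52 |
| 2% | 6.08 | 0 | 1.52 | 3.04 |

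One death in an arm of 152 is 1/152 = 0.66 percentage points. With so few events, one or two classifications can create or remove the observed difference between arms.

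**The case against.** The best case for the plan has several parts.

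*The definition is printed directly beneath the label, and Section 1 is only a short list.* An attentive reader of the protocol is not misled. This stands for the protocol, but a results table usually carries the label alone, and the label is the broader of the two.

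*Surgery-related death is a defensible measure of a transection technique in patients with cancer.* This stands. It is a reason to report it under its own name with a stated rule, and not as 90-day mortality.

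*With so few deaths, chance dominates under any definition.* This also stands. The illustration shows how much weight each classification carries; it does not show damage peculiar to this definition. An all-cause count would be just as sparse, but it would not depend on attribution.

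Some stronger readings are tempting and are not supported:

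- A reader might infer that site staff who know the arm classify the deaths. The protocol does not say who does. The inference rests on the display of the arm at registration and on the absence of any described blinding or adjudication. The contents of Section 15 (Organization) were not in the text available, and committee remits may be set out there.
- A reader might infer from Section 11.3 that deaths after day 30 go unrecorded. That section limits notification, while Section 9 lists mortality as a study parameter without restriction and Section 11.1 includes events leading to death. What is shown is that the endpoint need not count some of these deaths, not that they are lost.
- A reader might infer that vital status at day 90 is already secured. Follow-up runs to 6 months, with imaging at 1 and 6 months, but no day-90 contact is scheduled and the protocol does not state that vital status will be known.

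**Conclusion.** The point holds as a mismatch between the label and the definition of a secondary safety endpoint, made worse by the lack of a rule for relatedness. As written, the figure reported as 90-day mortality can be lower than all-cause mortality and depends on a causal judgement in a trial that describes no blinding.

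A reader might go further and conclude that deaths will be under-counted. The documents do not show that: the shortfall cannot be computed and is zero if every death by the cut-off is classed as surgery-related. Nor is bias between arms demonstrated; it is only left possible.

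The scope is limited. This is one of 18 secondary endpoints in Section 12, and no stated decision rule depends on it. The primary comparison of grade B/C fistula and the sample size are unaffected. The definition should still be corrected, because the trial's stated aim is safety and the correction is cheap.

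**What to change.** 1. In Section 12, define endpoint 17 as death from any cause from the operation date through postoperative day 90. This also puts label and definition in the same time unit.
2. Record on the case report form the date of every death to day 90, whatever its cause and whether or not Section 11.3 requires it to be notified.
3. Keep surgery-related death as a separately labelled supportive count, with a written definition of relatedness and a named adjudicator, preferably one who does not know the arm.

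The cost is a change of wording and a little data checking. Section 9 already lists mortality without a cause restriction. As no day-90 contact is scheduled, status at day 90 has to be read back from the 6-month follow-up, and patients who miss that visit will need a query to the site. The primary analysis and the sample size do not change.
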